### Study setting

The PEPPERMINT study will be conducted as a single-centre study at the University Hospital Ulm in Germany. The hospital is a tertiary care and academic hospital where about 30,000 anaesthesia procedures are performed annually, including a broad spectrum of surgical disciplines and interventions. To establish a data processing pipeline for imaging data and to integrate artificial intelligence (AI) algorithms into the study setting, an interface between the ultrasound devices and the hospital´s internal Picture Archiving and Communication System (PACS) has already been established. To bundle the expertise in image processing, collection, and processing of big data, the departments of anaesthesiology and radiology cooperate for this study.

The members of the study group are predominantly physicians and specialists in the fields of anesthesiology and radiology. The leader of the research group “Experimental Radiology”, who holds a formal background in engineering, is part of the study team. His expertise lies in machine learning, deep learning, and computer vision, with a focus on medical imaging applications. Another group member holds a master’s degree in medical informatics and has substantial experience in machine learning for perioperative risk prediction. The study team is completed by Master’s and PhD students from the Department of Radiology with a background in computer science and engineering

In addition to specialised personnel, high computing capacity for fast processing and reliable storage is necessary to develop the model and will be provided by the involved departments.

As the study is designed to build decision-support systems, on-site evaluation is planned as a subsequent step, which will be covered by a separate study. The data is evaluated offline without direct interaction between medical staff and the AI algorithm. Consequently, no feedback loop is planned in this phase.

### Eligibility criteria

Adult patients (≥18 years) of all sexes are eligible for the study.

Patients must meet the following **inclusion criteria**: Scheduling for elective surgical procedures under general anaesthesia with a planned overnight hospital stay, and written informed consent by patients.

If they meet any of the following **exclusion criteria**, they will not be included in the study: Younger than 18 years of age, outpatient surgery, planned postoperative admission to intensive care unit (ICU), need for intensive care treatment before surgery and emergency surgery.

**Secondary exclusion criteria** are: Unplanned hospital discharge/transfer on the day of surgery, which does not allow examination of the primary outcome; cancellation/postponement of index surgery; and immediate unplanned postoperative admission to the ICU due to an intraoperative complication.

Furthermore, the **Inclusion criteria for input data** are: At least two adjacent ribs and the pleura or corresponding pathologies (e.g., pneumothorax, pleural effusion) must be visible on the ultrasound image. The ultrasound examination must cover all 12 defined areas (details in chapter “Study measures”)**.**

The **exclusion criteria for input data** are: Ultrasound images on which the leading structures ribs and pleura or alternative pathologies cannot be depicted, or incomplete visualisation of the 12 previously defined examination areas in the thoracic region, e.g., in the case of immobile patients or inaccessibility due to a bandage or drains. Importantly, decisions regarding potential exclusion due to poor image quality will not be made by the examining physician, but rather by an independent, blinded radiologist, thereby minimising the risk of subjective selection bias.

Clinical data is collected from patients throughout their hospitalisation. An employee who is not involved in data collection will carry out a plausibility check and random comparison with the medical records at regular intervals. Implausible data is removed from the data record.

Patients who cannot be visited postoperatively and for whom no endpoint could be defined are excluded from the study; however, their data may be used for secondary analyses. Incomplete pre-operative routine data in the electronic patient record are not a reason for exclusion if the patient can be visited postoperatively

### Recruitement and informed consent

The University Hospital Ulm is a tertiary care hospital where about 30,000 anaesthesia procedures are performed annually. The PEPPERMINT study evaluates a general surgical population; therefore, eligibility criteria were set as low as possible. Approximately 50 patients are seen in the pre-anaesthesia outpatient clinic for preoperative evaluation each working day, of which about 80% will fulfil the inclusion criteria. The abovementioned 3 risk groups, according to the ARISCAT score, will be recruited equally, which means that after about 60 patients in one risk group, it will be paused, and the other risk groups will be prioritized until the same number is present in all risk groups. The equipment and staffing of the recovery rooms and the existing expertise in lung sonography allow the inclusion of 3–5 patients daily so that patient recruitment should be possible without any problems within one year.

Informed consent from trial participants or authorised surrogates will be obtained by a physician from the Department of Anaesthesiology and Intensive Care Medicine of the University Hospital of Ulm. The informed consent discussion will be part of the scheduled informed consent discussion for general anaesthesia. According to the usual routine preoperative procedure, the optimal anaesthesia for the patient is planned based on previous diseases, previous anaesthetic and surgical procedures, and personal preference. In case of doubt, the senior physician will be consulted. If the inclusion criteria are met and the patient gives consent, an informed consent discussion about the PEPPERMINT study will take place. Written informed consent will be obtained from the physicians, who will explain the hospital’s policy on data collection and storage, the general process, and the goals of the study. Additional consent for the collection of participant data, which is routinely obtained during standard pre-, intra- and postoperative anesthesiologic care, will be obtained as well.

A participants schedule is shown in Fig 1.

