### Sample size

Predicting POPC for the clinician is difficult on a case-by-case basis. Therefore, several scoring systems have been developed in the past. The most common of these, the ARISCAT score, has an AUROC of 0.83 [15]. It should be noted that the current literature does not provide any further metrics such as area under the precision-recall curve (AUPRC) or F1 score on the ARISCAT [15,16]. We therefore used the AUROC as the reference metric. The model we aim to create should be significantly better than the ARISCAT score and thus have at least an AUROC of 0.93. Achieving this seems realistic since, in the preliminary work of our research group, prediction models for various postoperative complications have already been created, whose predictive accuracy is in this range [17,18]. With a significance level of 0.05 and a power of 80%, 512 patients would be needed to create the database based on the method described by Hanley and McNeil for comparing ROC curves [19].

Patients are stratified according to the risk criteria determined by ARISCAT so that approximately equal numbers of patients are included in each of the low-risk (ARISCAT < 26 points), intermediate-risk (ARISCAT 26–44 points), and high-risk (ARISCAT ≥ 45 points) groups.

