### Model training and evaluation

The primary model development will be based on a dataset of 512 patients. Within this cohort, we will implement stratified k-fold cross-validation (typically 5- or 10-fold, depending on the final class distribution) where possible to assess model robustness and mitigate overfitting. Image-based deep learning models require extensive computational resources, therefore, cross-validation will be applied more selectively. We will therefore use a fixed training/validation/test split for imaging data, ensuring non-overlapping patient groups. Early model experiments will be conducted using internal validation on the training data with hold-out validation to optimize architecture and hyperparameters. Final model evaluation will be performed on an independent hold-out test set.

This hold-out test set will be compiled prospectively during the course of the study after model development, using newly enrolled patients not included in the training dataset. This temporal separation will ensure unbiased performance evaluation of the final model.

Model performance will be evaluated on the independent hold-out test set using several complementary performance metrics. These will include the area under the receiver operating characteristic curve (AUROC), the area under the precision-recall curve (AUPRC), overall accuracy, sensitivity, specificity, F1-score, as well as positive and negative predictive values. Calibration will be assessed using appropriate measures, such as the Brier score, Hosmer-Lemeshaw-Test and calibration curves. Clinical decision-making utility can additionally be evaluated using decision curve analysis (DCA).

Importantly, our models are designed to output individualized risk probabilities, not dichotomous predictions. As such, the selection of a cut-off point for potential clinical decision-making will be a post-modelling step, and risk thresholds for high-risk patient classification will not be predefined. Instead, various thresholding strategies will be explored post hoc, including Youden’s index (for balanced sensitivity and specificity), cut-offs optimized for specific clinical priorities (e.g., maximizing sensitivity), and thresholds guided by DCA.

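### Equal ARISCAT thirds give an enriched case mix, but the article plans absolute risks, predictive values and a clinical threshold with no described correction and no record of the natural mix

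*Protocol article*

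**What the plan says.** Under Recruitement and informed consent: "The PEPPERMINT study evaluates a general surgical population; therefore, eligibility criteria were set as low as possible". The same paragraph fixes the quota, "The abovementioned 3 risk groups, according to the ARISCAT score, will be recruited equally", and gives the mechanism: "after about 60 patients in one risk group, it will be paused" while the other groups catch up. The Sample size section repeats it: "Patients are stratified according to the risk criteria determined by ARISCAT so that approximately equal numbers of patients are included".

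Under Model training and evaluation, "our models are designed to output individualized risk probabilities, not dichotomous predictions". That section lists PPV, NPV, Brier score, calibration curves and decision curves, with cut-offs to be explored afterwards by Youden's index, clinical priority or decision curves. Objectives adds an optimal intervention threshold in case the model is applied clinically, and makes the lung-ultrasound model the primary objective. The only weighting named is outcome-class weighting, under Addressing overfitting and class imbalance. The SAP is cited as S3 File and is not shown.

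**The concern.** Pausing groups is needed only if the natural mix is unequal. The article's ARISCAT table suggests that high risk is scarce among eligible patients: age 51-80 (3) + upper abdominal incision (15) + surgery over 3 hours (23) = 41 points, still below the high-risk limit of 45. Emergencies (8 points) and planned ICU admissions are excluded. Equal thirds are therefore very probably an enriched sample.

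Enrichment is a legitimate way to develop a model. However, PPV, NPV, net benefit and data-driven cut-offs depend on case mix, and so do the predicted risks of a model that does not contain the variable used for selection. Reported unadjusted, they describe the quota sample and not the patients who will pass through the recovery room. The Introduction wants a score that finds patients at risk and also avoids overtreatment, and both depend on these quantities. Unlike an analysis detail, the natural ARISCAT mix has to be collected during recruitment; an SAP cannot supply it afterwards.

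**Working it through.** **Inputs from the article.** Equal thirds (512/3 = about 171 per group). POPC in the preliminary cohort 111/259 = 43%, with no ARISCAT mix given. Literature AUROC of ARISCAT 0.83. The sample size of 512 plays no part in this check.

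**Not in the article, hence assumed.** The natural mix (low/intermediate/high) and POPC risk per group.

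**1. Predictive values.** Assume group risks of 20/40/69%, chosen so that thirds give (20+40+69)/3 = 43%. Source prevalence is p = Σ(share × risk):
- 50/35/15: 0.100 + 0.140 + 0.1035 = 0.3435
- 80/15/5: 0.160 + 0.060 + 0.0345 = 0.2545

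PPV = se·p / [se·p + (1−sp)(1−p)], with se = sp = 0.85 held fixed as a simplification:
- thirds: 0.3655/(0.3655 + 0.0855) = 0.81
- 50/35/15: 0.2920/(0.2920 + 0.0985) = 0.75
- 80/15/5: 0.2163/(0.2163 + 0.1118) = 0.66

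NPV moves from 0.883 to 0.915 and 0.943. With lower group risks (2/15/45%), prevalence is 20.7% in thirds against 6.1-13.0% in the source, and PPV is 0.60 against 0.27-0.46.

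**2. Predicted risks.** The imaging-only model estimates P(POPC | image), which averages over ARISCAT groups in the proportions present in the sample; the quota changes those proportions. A simulation of 600,000 patients (continuous ARISCAT plus an imaging signal, assumed mix about 74/21/5, three risk levels) fitted logistic models on equal thirds and applied them to the source mix:

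| Mean risk in source | Level 1 | Level 2 | Level 3 |
|---|---|---|---|
| Observed | 0.095 | 0.211 | 0.284 |
| Imaging-only, unweighted | 0.179 | 0.355 | 0.396 |
| Imaging-only, weighted | 0.094 | 0.213 | 0.281 |
| With ARISCAT variables, unweighted | 0.095 | 0.213 | 0.280 |

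The imaging-only model overstates risk and weighting repairs it. The model containing the ARISCAT variables needs no repair.

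**3. Thresholds and net benefit.** Even for that combined model, thirds against source, the Youden cut-off was 0.231 vs 0.087, 0.419 vs 0.214 and 0.454 vs 0.287. Net benefit at a 20% threshold was 0.134 vs 0.032, 0.319 vs 0.110 and 0.353 vs 0.162.

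**4. AUROC of ARISCAT.** Continuous score in the simulation, thirds against source: 0.803 vs 0.769, 0.814 vs 0.761, 0.766 vs 0.702. For the three-level category over the assumed mixes and group risks, source minus thirds ranged from −0.10 to +0.03. The direction is not fixed.

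**5. Cost of weighting.** The weight for a group with source share s is s/(1/3) = 3s, and the effective fraction is 1/(3Σs²):
- 73/22/5: 1/(3 × 0.5838) = 0.57
- 59/30/11: 1/(3 × 0.4502) = 0.74

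**The case against.** Several stronger readings are tempting, and the documents do not support them.

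- *The trial analyses its sample as if it were the general surgical population.* The sentence about that population explains broad eligibility and makes no analysis claim. Weighting may be in the unseen SAP. This stands. What remains is that the article describes no tally of eligible patients, which weighting would need.
- *All predicted risks are wrong.* Selection on predictors that a well-specified model contains leaves conditional risk unbiased. This stands for a clinical or combined model with the ARISCAT items, but does not help the imaging-only model.
- *The comparison with ARISCAT is invalid, or the quota inflates ARISCAT's AUROC.* Both can be measured in the same patients, and that paired comparison is valid for the equal-thirds mix. The 0.83 enters only the sample-size argument, and the shift has no fixed sign.
- *PPV collapses to 36%.* That needs 9% prevalence. The article's 9-40% range reflects procedure and definition, not the quota.
- *The score will flag too many patients.* Overstated imaging-only risks point that way. In the simulation, however, the combined model's Youden cut-off was higher in thirds than in the source, which points to flagging fewer.
- *The late-enrolled test set has a distorted mix.* Whether the quota applies to it is not stated.

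It is also fair that evaluation is offline, cut-offs are exploratory, on-site evaluation is a separate study, and further cohorts are planned in which recalibration is possible. That lowers the urgency. It does not recover a natural mix that was never recorded.

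**Conclusion.** The point holds in a limited form. Equal thirds make the study's case mix differ from the population it says it evaluates, and the shown text plans absolute-risk outputs and a threshold for clinical application without correction. Affected are the imaging-only model's predicted risks and, for all models, PPV/NPV, net benefit and data-driven thresholds. AUROCs are valid for the equal-thirds mix, but should not be read as general-population values or set against 0.83.

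The size rests on assumptions throughout. With risks giving 43% POPC in thirds, the PPV loss is 0.06 to 0.15 over the mixes tried. It is larger if group risks are lower and steeper. In one simulated setting the imaging-only mean risk was nearly doubled (0.179 against 0.095). This is an inexpensive improvement to make while recruitment is open, not a flaw that invalidates the study.

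**What to change.** Either of two changes would do.

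1. From now on, tally the ARISCAT group of every eligible clinic patient; the recruiting checklist already carries the score. Weight by source share over study share when fitting or recalibrating the imaging-only model, and when computing calibration, PPV/NPV, decision curves, thresholds and both AUROCs. Show unweighted and ARISCAT-stratified results alongside.
2. Enrol the temporal hold-out set consecutively without the quota, and say so. This works only if the hold-out is the later-enrolled set of Model training and evaluation, not the split of the dataset described under the three predictive models.

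Cost: scoring about 40 eligible patients a day (80% of 50) when 3-5 can be enrolled, plus weighted analysis code. The Trial status section reports 150 of 512 included, so for that period the source mix must be scored retrospectively or assumed equal to the later one. Intervals widen: effective sample size is roughly 57-74% of nominal under the assumed mixes of 73/22/5 and 59/30/11. The weights do not correct selection by consent, staffing or image quality.

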**Fig 1 pone.0329076.g001:**
[figure not shown]
SPIRIT schedule PEPPERMINT trial. Schematic diagram presenting the schedule for participants, based on SPIRIT schedule; LUS = Lung ultrasound; POPC = postoperative pulmonary complications.

### Study measures

Study-related measures to acquire the imaging data include performing a standardised lung ultrasound on each included patient immediately postoperatively in the recovery room or post-anaesthesia care unit (PACU). Sonographic examination of the lungs is a common, noninvasive bedside procedure. It can be performed without additional positioning in supine position and takes approximately 5 minutes. The examination is performed using a standardised, previously published method [13]. Thereby, a convex probe (5 MHz) and a predefined preset of the ultrasound device (the default “lung” preset of the device) are going to be used. Each hemithorax will be divided into 6 areas, separated by the anterior and posterior axillary lines (anterior, lateral, and posterior) and a superior and inferior area. For each patient, 12 pictures and 12 videos, one in each area, will be captured. This 12-zone protocol showed the highest intra-class correlation coefficient compared to other protocols [14]. A graphical representation of the areas can be found in Fig 2.

**Fig 2 pone.0329076.g002:**
[figure not shown]
Graphic representation of the lung ultrasound areas. Lung ultrasound will be performed in 12 areas, 6 in each hemithorax. Areas are separated by the anterior and posterior axillary line into an anterior, lateral and posterior zone and a superior and inferior area.

The criteria for including imaging data are described above (“Eligibility Criteria”). If these conditions are not met, the interpretability of the ultrasound is considered insufficient.

To maximize inclusiveness and minimize selection bias, operators are encouraged to adjust technical parameters (e.g., depth and gain) during image acquisition in order to meet these quality criteria. A convex transducer was selected to allow visualization of deeper structures across a wide range of patient anatomies.

The performing physicians are experienced in perioperative medicine and critical care and will be trained in ultrasound methodology before the start of the study.

After transmission and storage in the PACS of the Department of Radiology, image pre-processing and artifact correction are performed before the data serves as input for the machine learning model. Images are not labeled by human experts; only the pre-defined endpoint POPC serves as labels for the imaging data.

The clinical data obtained for the study correspond to parameters routinely collected during anesthesiologic preoperative evaluation, the course of anaesthesia during surgery, and postoperatively in the recovery room. Plausibility checks are carried out on the numerical data; if these deviate from the valid value range, they are removed. Missing data may be imputed by different methods as described below.

Based on the collected data and the outcome parameters (description in chapter “Outcome”), machine learning algorithms will be trained to predict POPC by outputting an individual patient’s percentage risk of suffering a postoperative pulmonary complication.

### Modifications, adherence and concomitant care

Regarding the study protocol, the following scenarios allow a change in the study protocol: (1) In case of patient withdrawal of consent, the study protocol will be stopped immediately, and the patient will be excluded from the study. (2) If it is not possible to perform an ultrasound examination that meets the abovementioned quality requirements, the patient will be excluded from the study. (3) Postoperative lung ultrasound will take place in the recovery room; dates might be rescheduled depending on the postponement of the surgery. (4) Postoperative visits on the normal ward will be on postoperative days 1,3 and 7. If the patient is discharged from the hospital or transferred to another hospital within the first 7 days, the study ends on the day of discharge.

To improve workflow, the recruiting anaesthetist in the pre-anaesthesia outpatient clinic receives a simple checklist with eligibility criteria and the ARISCAT score (S1 File), and study information will be handed to patients in the waiting area. To improve adherence to the lung ultrasound protocol in the recovery room, a group of selected anaesthetists will undergo personal training in ultrasound methodology and receive detailed instructions in written form, which are also attached to the ultrasound device. Additionally, pocket cards with brief instructions will be distributed among the responsible physicians.

Postoperative ward visits will be performed by qualified study nurses and trained medical students with a tablet to simplify the visits and enhance data management.

During the trial, the patient will undergo routine perioperative care as per standard. Therefore, the patient receives the concomitant or intervention as per his physicians’ decision, and no concomitants or interventions are prohibited during the trial. Relevant information regarding POPC that results from postoperative diagnostics or interventions will be recorded. Supposed complications that have not yet been treated are noticed during the postoperative visit. In that case, the study staff will inform the responsible ward physician to initiate any necessary therapy.

